## Abstract

**Background:**

Gastroscopy procedures are frequently performed under general sedation to minimize discomfort. Patients who refuse a sedative injection may experience more discomfort and adverse reactions such as pain and nausea. These instances reduce patient compliance and willingness to participate in future procedures. Acupuncture has been shown to have an anti-nausea and analgesic effect; however, there is limited data available that demonstrates the efficacy of acupuncture when applied before gastroscopy.

**Methods:**

A total of 60 participants will be randomly assigned to the electroacupuncture (EA) group and the sham electroacupuncture (SEA) group at a ratio of 1:1. Acupuncture treatment will be performed before gastroscopy for a duration of 30 min. All patients will complete detailed questionnaires at 30 min and 7 days post-procedure to record the severity of their symptoms. The primary outcome will be the average of 4 standard visual analogue scale (VAS) scores in the categories of nausea, vomiting, throat discomfort, and agitation as reported by the patient. The secondary outcomes will be patient’s anxiety level as recorded by the 6-item short form of the State-Trait Anxiety Inventory (STAI-S6) and Amsterdam Pre-Operative Anxiety and Information Scale (APAIS), preference in a future endoscopy, pulse oxygen saturation (SpO2), heart rate (HR), and blood pressure (BP). Anxiety scales will be assessed before and after acupuncture; others will be completed at 30 min and 7 days post-procedure. The duration of the gastroscopy and the number of biopsies will be recorded after operation.

**Discussion:**

This randomized controlled trial will explore the feasibility of the further clinical application of electroacupuncture for the improvement of patient discomfort during gastroscopy without systemic sedation.

**Trial registration:**

ChiCTR2000040726. This trial has been approved by the Ethics Committee of Shanghai Municipal Hospital of Traditional Chinese Medicine (2020SHL-KY-11). Registration date 12 August 2020.

## Introduction

### Background and rationale {6a}

Upper gastrointestinal endoscopy (gastroscopy) is one of the most common diagnostic and therapeutic methods for assessing upper gastrointestinal diseases [1]. Gastroscopy is the first choice for clinical examination of upper gastrointestinal diseases because physicians can directly observe the inspection site and perform pathological biopsy and ligation on the diseased tissue in real time [2]. Due to the aging population and modern dietary changes, the average number of gastroscopies performed annually has sharply increased over the past few decades [3].

The strong stimulation from gastroscope insertion can often induce a gag reflex, which causes throat discomfort and nausea. Unmedicated patients also experience anxiety, increased blood pressure, and tachycardia during gastroscopy procedure. To curtail these symptoms, gastroscopy under general anesthesia is widely used. However, the use of anesthesia is costly and associated with inhibited cognitive function and mental decline. Moreover, the post procedural impairment affects a patients’ ability to drive and return to work immediately afterwards [4]. That is why approximately half of Chinese gastroscopy patients decline general anesthesia during gastroscopy [5, 6]. We therefore need to identify a safe and efficacy method to reduce adverse events during gastroscopy and offer patients a palatable alternative to sedation. Acupuncture analgesia has its unique advantages. Clinical trials have confirmed that preoperative acupuncture can reduce anxiety, decrease the use of anesthetic drugs, relieve nausea and vomiting, and shorten hospital stays [5–8]. Acupuncture during the perioperative period can help restore intestinal function and reduce postoperative pain [9, 10]. Studies have reported acupuncture analgesia as a successful alternative to pharmacological sedation during gastroscopy; however, the actual benefits still require further studies to corroborate [11, 12]. Therefore, high-quality randomized clinical trials are needed to re-validate previous findings and develop a clinical trial of electroacupuncture to reduce patients’ discomfort during standard gastroscopy.

### Objectives {7}

We designed a rigorous randomized controlled clinical trial using a single-center, patient- and assessor-blinded placebo-controlled research method to evaluate the impact of electroacupuncture (EA) on the discomfort of patients undergoing gastroscopy. We aim to observe whether EA can reduce the discomfort of patients during gastroscopy; the results will help provide evidence for whether EA is an effective therapy to reduce patient discomfort during general gastroscopy.

### Trial design {8}

This RCT is a single-site randomized placebo-controlled trial. It will be implemented in Shanghai Municipal Hospital of Traditional Chinese Medicine. All eligible patients will be randomly assigned to the electroacupuncture group (EA) or the sham electroacupuncture (SEA) group in a 1:1 allocation ratio. All patients must sign the informed consent form before they are enrolled in the trial. The research process flow chart is detailed in Fig. 1. In this trial, the Consolidated Standards of Reporting Trials (CONSORT) [13] and acupuncture reporting guidelines, Standards for Reporting Interventions in Clinical Trials of Acupuncture (STRICTA) [14], will be followed.

**Fig. 1 Fig1:**
[figure not shown]
Flowchart of this study

## Methods: participants, interventions, and outcomes

### Study setting {9}

All eligible participants will be recruited through the outpatient clinic or inpatient, hospital-based WeChat advertising, and posters in the Shanghai Municipal Hospital.

### Eligibility criteria {10}

#### Inclusion criteria

Patients who meet the following conditions will be included:
18–70 years old, male or femalePatients willing to undergo gastroscopy with local anesthesiaPatients with clear consciousness and can answer the questions, understand the scales, and complete the assessmentPatients who agree to participate and sign a written informed consent

#### Exclusion criteria

Patients who meet any of the following conditions will be excluded:
Patients with mental disorders or severe cognitive impairments who cannot participate in cooperationPatients with a history of bleeding disorders or who currently use warfarin or low-molecular-weight heparinPatients who cannot receive acupuncture for reasons such as infections around the acupuncture points or allergy to acupuncture needlesPatients who have received acupuncture treatment in the past 6 monthsParticipants in other clinical trials that may interfere with the primary endpoint

### Who will take informed consent? {26a}

All participants will be recruited by advertising through online and offline recruitment channels in Shanghai Municipal Hospital. People who need gastroscopy and are interested in participating can contact the researcher by calling or adding the WeChat. We will evaluate according to the inclusion and exclusion criteria. All participants will be clearly informed about the potential benefits and risks of the trial before they sign the informed consent.

### Additional consent provisions for collection and use of participant data and biological specimens {26b}

Not applicable.

### Interventions

#### Explanation for the choice of comparators {6b}

In this trial, all participants will receive the electroacupuncture or sham electroacupuncture before the gastroscopy. We will adopt the superficial acupuncture in the non-acupoints method. It has the advantages of good masking effect, not easily perceived by the patient, and a higher feasibility of operation.

#### Intervention description {11a}

All participants will receive the electroacupuncture or sham electroacupuncture before the gastroscopy. They will then undergo standard upper gastrointestinal endoscopy procedures. Patients in both groups will be discharged within 1 h after the endoscopy, which includes a 30-min observation period, a preference for future endoscopy assessment and blinding assessment. The acupuncture methods are described in Table 1. To maintain blinding, patients will be asked to wear an eye-patch and receive treatment in a supine position in an isolated space with limited communication with the acupuncturist. The acupuncturist will disinfect the patient’s skin with 75% alcohol cotton balls before treatment. Acupuncture treatment will last 30 min. After removing the needle, researchers will use a clean cotton ball to compress the acupoint to prevent bleeding. A total of 8 points will be used. Table 2 summarizes the acupoints and rationale.

**Table 1 Tab1:** Treatment methods of electroacupuncture and acupoints

	EA group	SEA group
Acupoints	Hegu (LI4), Neiguan (PC6), Zusanli (ST36), Liangqiu (ST34)	Non-acupoints as shown in Table 3
Depth of insertion	10 mm:LI4 PC6;30 mm:ST36 ST34	Superficial acupuncture
Needle type	Steel needles (Wuxi Jiajian Medical Co. Ltd. Wuxi, China)	The same as EA group
Needle sensation	With de-qi sensation	Without de-qi sensation
Electric stimulation	Two pairs of needles:	Two pairs of needles:
	LI4–ST36 (bilaterally)	LI4–ST36 (bilaterally)
	Connected to CMNS6-1 (Wuxi Jiajian Medical Device CO., China)	Connected to CMNS6-1 (Wuxi Jiajian Medical Device CO., China)
	Deliver continuous wave-type low-frequency 2 Hz and current of 2 mA	No electrical current delivered

*EA* electroacupuncture, *SEA* sham electroacupuncture

**Table 2 Tab2:** Acupoint selection and rationale based on traditional Chinese medicine

Acupoint	Location	Traditional Chinese medicine indication	Suggested technique
LI4 (Hegu)	Dorsum of hand, at the level of the midpoint of the second metacarpal bone, between the first and second metacarpal bones	Relieve visceral pain	Needle perpendicular,0.5–1.0 cun
PC6 (Neiguan)	Palmar aspect of the forearm, between the tendons, 2 cun away from the transverse crease of the wrist	Reduce nausea and stomach pain	Needle perpendicular,0.5–1.5 cun
ST36 (Zusanli )	Antero-lateral leg, 1 middle-finger breadth next to the anterior crest of tibia, 3 cun under the depression lateral to the patellar ligament	Reduce nausea and stomach pain	Needle perpendicular,1–2 cun
ST34 (Liangqiu)	2 cun above the bottom of the patella, on the line between the anterior superior iliac spine and the lateral end of the bottom of the patella	Relieve stomach pain	Needle perpendicular,1–1.2 cun

##### The electroacupuncture group

Participants in the treatment group will receive EA treatment. The standard acupuncture method will be applied at 8 acupoints: bilateral Hegu (LI4), Neiguan (PC6), Zusanli (ST36), and Liangqiu (ST34). All acupoints were selected based on literature, clinical experience, and acupuncture textbooks. The acupuncture needles will be disposable sterile needles made of stainless steel (0.25 × 40 mm and 0.30 × 40 mm; Jia Jian, China). After insertion, needles will be manipulated using the lifting-thrusting and twirling technique. A pair of electroacupuncture apparatus (CMNS6-1, Wuxi Jiajian Medical Device CO, China) will be connected to 2 pairs of needles (LI4, ST36 bilaterally) to deliver a continuous wave, low frequency (2 Hz), and current of 2 mA.

##### The sham electroacupuncture group

In the control group, we will use the same acupuncture needles as used in the EA group but repurposed as placebo needles. The acupuncturist will perform superficial acupuncture on the non-acupoints detailed in Table 3 and shown in Fig. 2. All of the needles will be inserted using a needle tube to a superficial depth (2–3 mm) without invoking the sensation of “De-qi.” The electroacupuncture apparatus will be connected to 2 pairs of needles (LI4, ST36 bilaterally) for 30 min, but all indicators will be set to “0” to ensure no electrical current is delivered.

**Table 3 Tab3:** Non-acupoints positioning

Acupoints	Non-acupoints
Hegu (LI4)	1 cun beside Zhigou (SJ6), between the sanjiao channel and the large intestine channel
Neiguan (PC6)	In the middle of the medial epicondyle of the humerus and the styloid process of ulna
Zusanli (ST36)	3 cun below Yanglingquan (GB34), between the gallbladder and bladder meridian
Liangqiu (ST34)	3 cun below Zhongdu (GB32), between the stomach meridian and the gallbladder meridian

**Fig. 2 Fig2:**
[figure not shown]
Superficial acupuncture on the non-acupoints

#### Criteria for discontinuing or modifying allocated interventions {11b}

When acupuncture-related serious adverse reactions occur during the experiment or there is a failure to complete the study for any other reasons, we will record the details in a report for the early termination of the study.

#### Strategies to improve adherence to interventions {11c}

At the beginning of the trial, participants will be again informed of the experiment procedure. They can report their personal feelings at any time during the study and we will give corresponding feedback as appropriate to increase the interactivity and improve adherence to interventions.

#### Relevant concomitant care permitted or prohibited during the trial {11d}

Patients cannot eat 8 h before gastroscopy to ensure a fasting state.

#### Provisions for post-trial care {30}

At the end of the study, we will provide a subsidy to each subject.

### Outcomes {12}

#### Primary outcome

A visual analogue scale (VAS) will be used to evaluate the patient’s level of discomfort, which is a line segment from 0 to 10, with 0 indicating low and 10 indicating high discomfort. All patients will complete 4 detailed VAS at 30 min. The questionnaire will evaluate 4 areas of discomfort including nausea and vomiting, throat discomfort, bucking, and agitation. The primary outcome is the average score of the 4 VAS.

#### Secondary outcomes

The patient’s level of discomfort at 7 days post-procedure by using VAS. The four VAS including nausea and vomiting, throat discomfort, bucking, and agitation will present separately as secondary outcomes at 30 min and 7 days post-procedure.Cardiac-respiratory assessment

All patients’ pulse oxygen saturation (SpO2), heart rate (HR), and blood pressure (BP) measurements will be recorded prior to, during, and post-procedure. Then, each patient’s “double product” (DP) will be calculated at each point of the procedure, based on the systolic blood pressure (SBP) and heart rate (SBP×HR). DP is a useful prognostic tool for patients with poor cardiac function during exercise and rest, reflecting myocardial oxygen consumption and cardiac output during treadmill testing. A value of DP greater than 15,000 indicates cardiovascular stress. It is accepted that changes in cardiac output from baseline (preoperative) will reflect the level of stress experienced by patients undergoing the gastroscopy.
Anxiety level

A six-item short form of the State-Trait Anxiety Inventory (STAI-S6) and Amsterdam Pre-operative Anxiety and Information Scale (APAIS) will assess the degree of preoperative anxiety, postoperative anxiety, and 7 days post-procedure. These questionnaires are quick and simple for participants to complete, which is advantageous in time-restricted studies.
Preference in a future endoscopy

The questionnaire will ask patients whether they have undergone gastroscopy before, and then ask, “Do you have interest in taking acupuncture treatment for to avoid the post-operative discomfort before next gastroscopy?”
Safety assessment

Before participants sign the informed consent form, they will be informed that acupuncture clinical trials may have potential adverse events such as bleeding, hematomas, fainting, bruising, ecchymoma, and possible infection. All details of the adverse event will be recorded by the patients and doctors. Adverse events (AE) are rated as 1 (mild), 2 (moderate), or 3 (severe or medically significant). All details of AEs will be recorded in the case report form (CRF). At the end of the trial, we will analyze the impact of all events.
Blinding success assessment

After the gastroscopy procedure, researchers will evaluate the success of the blinding by asking participants the following question: “what kind of treatment do you think you have received?” The options are traditional acupuncture treatment, superficial acupuncture treatment, and uncertain. If participants do not choose “uncertain,” then the researcher will question the patient further for specific reasons.
Related to gastroscopy

The duration of the gastroscopy and the number of biopsies will be recorded after operation.

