### Participant timeline {13}

The timing of intervention and data collection is detailed in Table 4.

**Table 4 Tab4:** Schedule of enrolment, intervention, and assessments

Timepoint	Screening	Baseline	Intervention		Operation			Follow-up
			Before	After	Before	During	30 min after endoscopy	Day 7

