For patients, surgical procedures performed in hospitals are a strong stressor and can lead to an anxiety response. Excessive anxiety can affect immune mechanisms through the release of corticosteroids and may be associated with abnormal hemodynamics as a consequence of endocrine changes and activation of the central nervous system [22, 23]. A high level of preoperative anxiety will also reduce patients’ satisfaction with the procedure and increase the risk of postoperative nausea and vomiting [24, 25]. So, in this trial, we will focus on preoperative anxiety. The STAI-S6 and APAIS are reliable means of assessing patient anxiety [26, 27]. By using these questionnaires, we can quickly and accurately assess patients’ anxiety level in a few minutes.

Previous findings have shown that gastroscopy may bring a series of complications to patients with hypertension, such as myocardial infarction, cardiac arrest, and other complications [28]. Some research has shown that in patients older than 45 years, the risk of cardiovascular disease doubles with an increase in systolic blood pressure of 20 mmHg or a diastolic blood pressure increase of 10 mmHg [29, 30]. So, in our study, we will monitor BP before, during, and after gastroscopy, then analyze the correlation between DP and the primary outcome of VAS score to determine whether EA can reduce stress placed on the heart, and thus benefit elderly people with cardiovascular related diseases who need gastroscopy.

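### Heart rate, blood pressure and double product are first read after acupuncture, so change from the preoperative value the plan calls baseline would not measure the full effect of EA

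*Protocol article*

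**What the plan says.** Under Intervention description {11a}: "All participants will receive the electroacupuncture or sham electroacupuncture before the gastroscopy". The Abstract's Methods gives the length: "Acupuncture treatment will be performed before gastroscopy for a duration of 30 min".

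For the cardiac-respiratory assessment, Secondary outcomes says that SpO2, heart rate and "blood pressure (BP) measurements will be recorded prior to, during, and post-procedure". DP (systolic pressure × heart rate) is calculated at each of these points, and a value above 15,000 is taken as a sign of cardiovascular stress. The paragraph presents DP as a reflection of cardiac output, then closes with its rule for reading changes over time: "It is accepted that changes in cardiac output from baseline (preoperative) will reflect the level of stress experienced by patients".

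Table 4 (Participant timeline {13}) has separate columns for Screening, Baseline, Intervention (Before, After), Operation (Before, During, "30 min after endoscopy") and Day 7. The heart rate, blood pressure and SpO2 row is marked in the three Operation columns only.

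The Discussion gives the purpose of these data: "to determine whether EA can reduce stress placed on the heart".

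**The concern.** A baseline should precede anything the treatment can alter. Here the first cardiovascular reading comes after the full 30 min of EA or sham.

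On the protocol's own reasoning that reading could already differ between arms. The Background says that acupuncture before an operation can lower anxiety, and the Discussion links excessive anxiety to abnormal haemodynamics. If EA calms patients before the scope, their starting DP is lower, and a rise measured from that lower start gives EA no credit for the early reduction. At stake is the secondary question of whether EA lowers cardiac load during gastroscopy. There would also be no untreated value with which to check balance or gain precision, in a trial of 60 patients (60 / 2 = 30 per arm) that does not restrict comorbidities.

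**Working it through.** The plan states no figure for DP, so there is none to reproduce. The check has two parts.

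**1. Timing, from Table 4**

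| Row | Columns marked |
|---|---|
| EA, SEA | Intervention-Before, Intervention-After |
| STAI-S6, APAIS | Intervention-Before, Intervention-After |
| HR, BP and SpO2 | Operation-Before, Operation-During, 30 min after endoscopy |

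The schedule has a pre-acupuncture slot and uses it for the anxiety scales but not for the cardiovascular readings. The text agrees with the table: Secondary outcomes says "measurements will be recorded prior to, during, and post-procedure", and the Discussion again places blood pressure around the gastroscopy. The preoperative value is therefore the Operation-Before value, taken after acupuncture.

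**2. What a change score from that value estimates**

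For each arm, let P be mean DP at Operation-Before and D mean DP during endoscopy. Let B be mean DP before acupuncture, equal in both arms in expectation because of randomisation. Count a reduction under EA as positive:

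- T = D(SEA) − D(EA), the total effect during the scope
- E = P(SEA) − P(EA), the part already present before the scope

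Change from the Operation-Before value: [D(SEA) − P(SEA)] − [D(EA) − P(EA)] = T − E.

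Change from a pre-acupuncture value: [D(SEA) − B] − [D(EA) − B] = T.

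The documents give neither T nor E. Assuming T = 1,000 DP units for illustration, the range is:

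| E as share of T | E | Change from Operation-Before (T − E) | Change from pre-acupuncture value (T) |
|---|---|---|---|
| −25% (EA raises DP beforehand) | −250 | 1,250 | 1,000 |
| 0% | 0 | 1,000 | 1,000 |
| 25% | 250 | 750 | 1,000 |
| 50% | 500 | 500 | 1,000 |
| 75% | 750 | 250 | 1,000 |
| 100% | 1,000 | 0 | 1,000 |

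The last row in assumed DP values: both arms start at 10,000 before needling. EA falls to 9,000 and reaches 13,000 during the scope; sham stays at 10,000 and reaches 14,000. The rise is 13,000 − 9,000 = 4,000 under EA and 14,000 − 10,000 = 4,000 under sham, so the change scores show no difference. DP during the scope differs by 14,000 − 13,000 = 1,000.

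A direct comparison of D between arms estimates T in every row without needing a baseline. A comparison of the proportions above 15,000 likewise subtracts nothing.

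**The case against.** The strongest reply is that the distorted analysis is not actually prescribed. The Statistical methods section {20a} names t-tests, rank-sum tests and χ² tests without saying whether absolute values or changes are compared, and that choice is often left to a statistical analysis plan, which is not shown. Secondary outcomes calculates DP at every point and gives an absolute threshold. The baseline sentence is a rationale about cardiac output, not an endpoint definition, and it labels its reference as preoperative. This stands: the bias is conditional on how DP is compared.

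Second, change from just before the scope answers a legitimate question, namely reactivity to the procedure. This also stands. T − E is a different quantity from T, and it misleads only if presented as the total effect of EA.

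Third, Table 4 in a condensed article may be incomplete. It omits the day-7 anxiety assessment that the text promises. For the cardiovascular readings, though, text and table agree, and neither mentions a reading before acupuncture. An analysis plan could choose the right comparison but could not recover a measurement that was never taken.

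A reader might go further and infer that a true reduction in cardiac load will be missed or even reversed. The documents do not support that. It would require change scores to be the comparison used, and E to equal T (missed) or exceed it (reversed). The protocol expects an effect on anxiety before the scope but gives no haemodynamic figure for it.

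**Conclusion.** The point holds in a conditional form. The documents show that the cardiovascular value called baseline is taken after randomisation and after treatment. If DP is compared between arms as change from that value, the comparison estimates T − E. The consequence runs from no loss (E = 0) to complete loss (E = T), with inflation if EA raises DP before the scope. The size cannot be fixed, because the documents give no DP, heart rate or blood pressure effect; the 1,000-unit illustration is an assumption.

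A direct comparison of DP during endoscopy, or of DP above 15,000, is not biased in this way. Because the arms are randomised, the missing pre-treatment value then costs only precision and a balance check. It would therefore be wrong to conclude that the cardiac comparison is bound to fail. The primary VAS outcome is unaffected. The change is still worth making, because the remedy is cheap and the cardiac question is a stated aim.

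**What to change.** - In Table 4, add heart rate, blood pressure and SpO2 at Intervention-Before, the slot already used for STAI-S6 and APAIS, and define that reading as baseline.
- Compare DP during endoscopy between arms by ANCOVA, with the pre-acupuncture DP as covariate.
- For patients already enrolled without the reading (Trial status gives February 2021 as the start of recruitment), compare DP during endoscopy directly between arms. Both analyses target T.
- Keep the Operation-Before reading, but report it as a post-acupuncture outcome. Label any change from it as reactivity to the procedure, not as the total effect of EA.
- Reword the baseline sentence in Secondary outcomes to match.

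The cost is one extra routine vital-sign reading per patient, at a visit that already takes place, and an edit to the table and text. The direct comparison for patients already enrolled needs no new data.

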### Plans to promote participant retention and complete follow-up {18b}

Patients will come to the hospital 1 week after gastroscopy to complete the final questionnaires. We will follow up and debrief patients at this time point. At the end, patients will receive a transportation subsidy.

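### The anxiety outcome is defined at pre-operative, post-operative and day-7 time points, but Table 4 and the abstract schedule both scales only on either side of the acupuncture session, before the gastroscopy

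*Protocol article*

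**What the plan says.** The protocol article states the timing of the anxiety assessments in three places.

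- **Secondary outcomes, Anxiety level.** STAI-S6 and APAIS "will assess the degree of preoperative anxiety, postoperative anxiety, and 7 days post-procedure".
- **Abstract, Methods.** "Anxiety scales will be assessed before and after acupuncture; others will be completed at 30 min and 7 days post-procedure". This separates the anxiety scales from the measures taken at 30 min and day 7.
- **Table 4.** The STAI-S6 and APAIS rows each carry two marks, under Intervention-Before and Intervention-After. Neither row has a mark under any Operation column or under Day 7.

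Four other statements bear on how to read these.

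- Participant timeline {13} gives Table 4 its status: "The timing of intervention and data collection is detailed in Table 4".
- The abstract fixes the order of events: "Acupuncture treatment will be performed before gastroscopy for a duration of 30 min".
- Section {18b} provides a one-week visit without naming the forms used: "Patients will come to the hospital 1 week after gastroscopy to complete the final questionnaires".
- The Discussion, after describing the harms of pre-operative anxiety, says: "So, in this trial, we will focus on preoperative anxiety".

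**The concern.** The article gives two different sets of time points for the same secondary outcome. The definition looks past the endoscopy to recovery and to one week. The schedule stops before the endoscopy begins. Both cannot be the plan.

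Three things are at stake.

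- If staff work from Table 4, two of the three time points in the outcome definition are not collected. No analysis plan can recover them.
- The score taken after acupuncture and before the endoscopy is the one that shows whether electroacupuncture changes pre-operative anxiety. The outcome definition does not name it.
- With two versions in print, the anxiety time point to be reported can be chosen after the results are known.

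**Working it through.** No formula or power figure is involved. The check sets the three statements side by side and counts time points.

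**Step 1: the columns of Table 4.** In order, the header reads Screening; Baseline; Intervention (Before, After); Operation (Before, During, 30 min after endoscopy); Day 7. That makes eight columns. The STAI-S6 and APAIS marks fall in columns 3 and 4.

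**Step 2: the three statements compared.**

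| Time point | Outcome definition | Abstract | Table 4 |
|---|---|---|---|
| Before acupuncture | within pre-operative | yes | yes |
| After acupuncture, before endoscopy | not separately named | yes | yes |
| Post-operative (after endoscopy) | yes | no | no |
| Day 7 | yes | no | no |

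**Step 3: the count.** The definition gives 3 time points: 1 before and 2 after the procedure. The abstract and Table 4 each give 2, both before the procedure, and 0 after it. With two scales, the definition implies 2 × 2 = 4 post-procedure completions per patient. The schedule provides for none.

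**Step 4: could the table have been misread?** The columns were recovered from a PDF, so a shifted mark is possible in principle. Two things argue against it. The secondary discomfort VAS row and the future-preference row in the same table do carry marks at 30 min and Day 7, so those columns came through intact. The anxiety rows also match the abstract's sentence exactly, and that sentence does not depend on table layout.

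**Step 5: could the wording be reconciled?** Post-operative might be read as after the acupuncture. Table 4 uses Operation for the endoscopy, which tells against that reading. Even if it were accepted, day 7 would still appear in the definition and not in the schedule.

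**The case against.** The best case for leaving the text alone is that two of the three places agree, that the Discussion points the same way, and that the outcome paragraph is therefore a loose sentence in a condensed article. There is something in this: the pre-procedure assessments are well supported. It does not explain the day-7 assessment, which is stated explicitly in the section that defines the outcomes and contradicted by the table that the article names for timing. Nor is this detail that an article leaves to a fuller document, because the time points are given here and they conflict.

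Several stronger readings are tempting but are not supported.

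- **That the post-procedure and day-7 anxiety data will be wholly missing.** This assumes that staff follow Table 4 and disregard the outcome definition. No case report form is shown, and the questionnaires at the one-week visit are not named, so the anxiety scales could be among them. The documents support only that these assessments are unscheduled and may not be collected.
- **That following the outcome definition would lose the contrast across acupuncture.** Both scheduled assessments precede the endoscopy and can fit under pre-operative anxiety, and the abstract and Table 4 state the pair explicitly. The risk is low. The fault is that the definition does not name the second assessment.
- **That APAIS cannot be rated after the procedure.** The article reproduces none of its items. The inference rests on the scale's name alone and forms no part of this point.
- **That the abstract also misplaces SpO2, heart rate and blood pressure.** Read literally, its remainder clause would put them at 30 min and day 7. The outcome definition and Table 4 agree on before, during and after the procedure, so this is a minor wording matter in the abstract.

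Adjusting for the pre-acupuncture score is a recommendation. The contradiction stands without it.

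**Conclusion.** The contradiction is real and rests on the current text alone. Two of the three anxiety time points in the outcome definition have no slot in the schedule or the abstract, and the scheduled assessment after acupuncture is not named in the definition. The consequence is conditional: if Table 4 governs what staff do, post-operative and day-7 anxiety will not be collected.

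The effect is confined to one secondary outcome measured on two scales. The primary VAS outcome, its analysis and the sample size are unaffected. The conclusion assumes that the marks in Table 4 sit where the recovered columns place them, which the abstract corroborates. It should be corrected, because unclear timing affects what is collected and a later analysis plan cannot repair that.

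**What to change.** 1. **State one set of time points** in the abstract, the Anxiety level paragraph and Table 4. Trial status says that recruitment began in February 2021, so first establish which anxiety forms have been given and when, and make the text consistent with that.
2. **Name the anxiety outcome** as the STAI-S6 and APAIS scores after acupuncture and before endoscopy. This is already scheduled and fits the pre-operative focus in the Discussion. Compare arms with a linear model that includes the pre-acupuncture score as a covariate, in place of the plain two-group tests in section {20a}. That score is already collected, so the adjustment needs no new data. With correlation ρ between the two scores, it multiplies the residual variance by about 1 − ρ²; the article gives no value for ρ.
3. **Settle the later time points** in one of two ways. Either add marks to Table 4 at 30 min after endoscopy and Day 7, where the VAS and preference questions are already completed, or delete post-operative and day-7 anxiety from the outcome definition. If APAIS is kept at the later time points, the authors should confirm that its items apply there.
4. While editing the abstract, limit the clause on 30-min and day-7 completion to the questionnaires.

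Deletion costs a text correction. Adding the assessments costs short forms (six items for STAI-S6; the article gives no item count for APAIS) at two contacts that already take place, and an amendment through the route the article describes. No change to the sample size or the primary analysis is needed.
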